#### Handling of Missing Data

Patterns and mechanisms of missing data will be examined. Missing data will be handled using multiple imputation under a missing-at-random assumption. The imputation model will include all analysis variables (primary and secondary outcomes, baseline covariates, treatment group, and cluster identifiers), as well as auxiliary variables associated with missingness, to improve the plausibility of the missing-at-random assumption. Approximately 20-50 imputations will be generated, with the final number guided by the proportion of missing information.

Patterns of missingness will be examined to distinguish monotone (eg, dropout after baseline) and nonmonotone patterns, and appropriate imputation methods will be applied accordingly. For the cRCT, potential differential attrition between the intervention and control groups and across clusters will be assessed and reflected in the imputation model.

Sensitivity analyses will compare imputed results with complete-case analyses and alternative assumptions (eg, pattern-mixture approaches) to evaluate robustness.

#### Exploration of Health Care Workers’ and Informal Caregivers’ Perspectives

Qualitative data collection will take place at the recruited sites in the same 6 European countries and Australia. The data will be collected through semistructured interviews with leaders, health care workers, and informal caregivers to explore their diverse challenges in everyday tasks and care situations, types of ethical stress, adverse events, situational support, needed adaptations, solutions to improve working and caring conditions, how they integrate and experience patient and user involvement, and the role of stakeholders in resilient service performance and in improving involvement. This will include 3-5 focus groups with leaders, 3-5 focus groups with health care workers, and 10 individual interviews with informal caregivers in each participating country (see Multimedia Appendix 2).

The interviews will be conducted in the informants’ native languages to allow for rich data and nuanced insights. The qualitative data will be analyzed using inductive thematic analysis [32], in which the data are analyzed inductively to allow themes and insights to emerge. The findings will be reported by the researchers in each country using a predefined, standardized template in English. This approach will allow for cross-country analysis of patterns across cases, as well as integration and comparison across health care systems and informant groups. Informants will be recruited in collaboration with the participating sites in all countries. Interviews will take place at the workplace for health care workers and leaders and at the preferred location of the informal caregivers. Focus groups will last approximately 2 hours each, whereas individual interviews will last approximately 1 hour each.

### Co-Design of the S4R Toolbox and Prototype Testing Phase

#### Overview

The second phase (WP3) will lead to the development of a digital S4R Toolbox for leaders to promote resilient performance and mental well-being among health care workers and informal caregivers. WP3 begins in month 5 and continues through month 30. The features and content of the S4R Toolbox will be developed based on findings from the first input phase, systematic literature reviews, and cross-country qualitative and quantitative data collection. Cross-country data from diverse settings will be used to provide an understanding of factors and challenges that are relevant across settings (residential care homes, home care services, and the hospital-to-home interface) and target groups (leaders, health care workers, and informal caregivers), ensuring that the S4R Toolbox provides value across the included older adult care settings. The development phase applies an iterative co-design methodology using an Agile software development process [33], in which a development team continuously develops the content and features of the S4R Toolbox by organizing 8 collaborative workshops (6 national and 2 transnational) with a co-design panel consisting of consortium partners and collaborators, as well as representatives of the target groups (3-5 health care leaders, 3-5 health care workers, and 3-5 informal caregivers), to ensure relevance and usability.

The S4R Toolbox includes 3 tools: (1) Mapping and Identification Tool (to increase awareness), (2) Reflection and Education Tool (to increase understanding), and (3) Reorganization Tool (to support reframing; Figure 1). While the S4R Toolbox is intended for leaders, the tools rely on the involvement of different stakeholders, including health care workers and informal caregivers, to ensure collaboration across organizational levels and stakeholder groups. All test sites will implement and evaluate the S4R Toolbox through a 1-year intervention program. The S4R Toolbox aims to bring about organizational- and system-level changes through leaders as change agents to improve working conditions for frontline health care workers and informal caregivers. Accordingly, the intervention requires sufficient time for these changes to take place.

#### Tool 1: The Mapping and Identification Tool

This tool will provide several reports and graphs based on data collected from different stakeholders (ie, informal caregivers, frontline leaders, and health care workers) to enable leaders to gain a comprehensive overview of the current status of their organization. The main input will be gathered through questionnaire responses from the involved stakeholders. The questionnaire will be intentionally developed for this tool and will pertain to 3 main areas identified through previous literature reviews: Supporting the Worker, Improving Working Conditions, and Improving Work Culture. The questions will be answered on a 5-point Likert scale and will address areas such as how well the unit fosters learning and professional growth, creates a balance between control and autonomy, develops a shared understanding of professional practice, and promotes communication and positive relationships at work.

Suitable graphs (eg, histograms and bar graphs) will be used to visualize the results, while natural language processing techniques will be used to facilitate leaders’ exploration of the findings. Presenting the data in multiple formats will further enhance the user-friendliness of the tool. The purpose is to provide leaders with a quick, easy-to-use overview of the current status of the unit as a basis for using tool 2.

#### Tool 2: The Reflection and Education Tool

Building on the same 3 themes addressed in tool 1, this tool is structured into 3 distinct learning modules: Supporting the Worker, Improving Work Conditions, and Improving Work Culture. Based on the scores obtained in tool 1, leaders are encouraged to begin with the module in which their unit demonstrates the strongest performance. Each module incorporates short informational videos, reflective questions, and brief learning scenarios depicting everyday work situations relevant to the thematic area. Through these activities, leaders, together with their staff, are expected to identify existing strengths and the underlying reasons for them.

The overarching aim is to enhance understanding of how work is carried out within the unit, identify resilient and effective practices, and promote improvement by learning from what works well. Once leaders have gained insight into successful practices, they are encouraged to translate this knowledge into targeted actions to address areas that require further development.

#### Tool 3: The Reorganization Tool

This tool addresses a well-known challenge in improvement work: the tendency to continually add new tasks and procedures without removing outdated ones. Over time, this can lead to overlapping practices and reduced system coherence. The aim of tool 3 is therefore to help units identify and safely discontinue practices that no longer add value.

The tool will include a function for gathering input from leaders, staff, and family members on activities they consider unnecessary or burdensome. Based on these insights, leaders will be provided with clear guidance and a structured action plan for removing practices in a responsible and transparent manner. The tool will also offer practical guidance on risk assessment, communication, and monitoring to ensure that discontinuation is carried out safely.

#### S4R Intervention Design Development Phase

Given the pace of work and the stressful environment of older adult care, the intervention design will be aligned with everyday work to reduce the likelihood that leaders will perceive the intervention as an additional stressor [34]. The S4R intervention will consist of 3 phases, each corresponding to 1 of the 3 tools in the S4R Toolbox. During each phase, frontline leaders will engage with different elements of the tool and participate in different activities (see Multimedia Appendix 3). The implementation of the intervention is planned to take 12 months. Six local learning collaboratives (including consortium researchers and co-researchers from the clinical setting) will be established, 1 in each European partner country, in addition to 1 principal learning collaborative comprising representatives from all 6 local learning collaboratives. Australia will have a separate learning collaborative because of time zone differences.

For each country, a designated intervention team consisting of consortium partners will be formed. The teams will be responsible for administering the local learning collaborative and coordinating the overall implementation activities throughout the intervention in their respective countries.

#### Sustainability of the S4R Toolbox

The S4R intervention design and Toolbox will be open access through the S4R Resource Bank, which includes self-directed instructions on how to implement the intervention. Furthermore, the infrastructure supporting deployment of the Toolbox will ensure server maintenance for 5 years after project completion. This period will also allow time to implement a successful exploitation strategy.

### Implementation, Evaluation, and Finalization Phase

#### Overview

The third phase (WP4) will implement and evaluate the use, relevance, effectiveness, and cost-effectiveness of the S4R Toolbox across the different health care systems involved (months 22-43; see Figures 2 and 4). Implementation of the S4R Toolbox will be carried out in line with the intervention design and the MRC guidelines [13,35-37] (see Multimedia Appendix 4). This design prioritizes the development of interventions that are both theoretically robust and practically adaptable to real-world conditions. The S4R intervention offers a coherent structure—with defined phases, tools, and recommended practices—while still enabling teams to tailor its components to their specific context, consistent with the MRC guidelines. The S4R Toolbox is intentionally flexible: although leaders are encouraged to follow the recommended structure, they may adjust the format, frequency, and integration of its elements to suit the needs and dynamics of their particular setting.

Implementation and evaluation will contribute to exploring the value of the S4R Toolbox in terms of usability, technical features, leadership support, performance, effectiveness, and cost-effectiveness, as well as provide input for the development of policy recommendations and theoretical frameworks. Evaluation of the S4R intervention will follow the study designs used in each country. Four analyses are planned for WP4: (1) process evaluation, (2) pre-post evaluation (test cases 2-4), (3) a cRCT (Norway and Finland, test case 1), and (4) cost-effectiveness evaluation.

A qualitative process evaluation will be performed [13]. Interviews with leaders, health care workers, and informal caregivers conducted in the initial phase of the intervention will be complemented by interviews conducted during and after the intervention period. Additionally, observations will be made during workshops to explore work processes and interactions among participants during implementation of the intervention. To minimize interference with implementation, we will develop standardized informational materials that will be used across all participating units. The researchers will limit their involvement to working directly with leaders through separate workshops and will not be present in the units when the Toolbox is applied in practice. This approach is intended to reduce researcher influence on everyday workflows and ensure that the Toolbox is used as intended by the local leadership. In addition, we will systematically document the contextual circumstances of each unit through context mapping and use standardized observation forms to record events or conditions that may have influenced implementation. These strategies will help differentiate between natural contextual variation and external factors that could interfere with the implementation process.

The data collected will contribute to exploring how the S4R Toolbox supports leaders, how health care workers and informal caregivers experience involvement, and whether capacity-demand challenges improve. In addition, the content of the Toolbox will be explored (eg, comprehension of the learning materials, factors important for sustainability, and levels of engagement and reflection), as well as the nonfunctional and quality aspects of the technical platform (eg, usability, tool design, and accessibility). The knowledge gained will inform further refinements to the Toolbox. Each participating site will include 3-5 focus group interviews with leaders, 3-5 focus group interviews with health care workers (nurses, physicians, and other health care workers), and 10 individual interviews with informal caregivers.

We will assess the effectiveness of the S4R Toolbox through a cRCT (test case 1), a pre-post evaluation (test cases 2-4), and a cost-effectiveness evaluation (test case 1). In both study designs, the primary outcome will be health care workers’ mental well-being, measured using the SWEMWBS. Secondary outcome measures include individual resilience, organizational resilience capacities, burnout, turnover intention, self-assessed health, and, for informal caregivers, family involvement in care and caregiver self-assessment. In addition, sick leave will be assessed using public sick leave records where available. The effectiveness, cost-effectiveness, and cRCT analyses of the S4R intervention will provide information for decision makers in organizations at both the national and European Union (EU) levels.

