### Objectives

Through the S4R digital Toolbox, the primary objective of the project is to support leaders in older adult care across Europe and Australia in improving resilience and mental well-being among health care workers and informal caregivers by integrating their perspectives and suggestions for improving working conditions. For the secondary objectives and research questions, see Table 1.

**Table 1 table1:** Secondary objectives and research questions.

Secondary objectives	Research questions
To map and identify factors associated with resilience and mental well-being among health care workers, informal caregivers, and leaders in older adult care across 6 European countries and Australia, and to integrate contextual factors, geographical settings, gender perspectives, and capacity-demand challenges.	How can resilience and mental well-being among health care workers, informal caregivers, and leaders in older adult care across different health care systems be understood, and what factors are important for promoting resilience and mental well-being in older adult care services?
To explore the needs and perspectives of health care workers and informal caregivers to support successful adaptation to changing working conditions, ethical dilemmas, and adverse events, and to identify potential solutions.	What needs and perspectives of health care workers and informal caregivers support successful adaptation to changing working conditions? What successful adaptations can be identified as solutions to challenges and changing working conditions across different older adult care settings?
To develop the digital S4R^a^ Toolbox for leaders to promote resilient performance and mental well-being based on the characteristics, needs, involvement, and improvement suggestions of health care workers and informal caregivers.	How can a leadership tool be designed and developed to promote resilience and mental well-being among health care workers and informal caregivers?
To implement and evaluate the use, relevance, effectiveness, and cost-effectiveness of the S4R Toolbox across different health care systems in 6 European countries and Australia.	What are the relevance, effectiveness, and cost-effectiveness of the S4R Toolbox for improving the resilience and mental well-being of health care workers?

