**Figure 3 figure3:**
[figure not shown]
Support4Resilience (S4R) test cases in different countries.

Test case 1 will be carried out in Finland and Norway, 2 countries with the most similar older adult care systems (eg, number of older adults receiving care services and home care services), where public home care services are common and are the responsibility of municipalities or counties [14]. Data will be collected, and the S4R Toolbox will be tested in public home care services across a variety of geographical locations (including rural areas), municipalities, and travel distances for health care workers and informal caregivers.

Test case 2 will take place in public residential care institutions and residential care institutions receiving public funding in Spain. Data will be collected, and the S4R Toolbox will be tested in the context of public residential care services. This context is common in several European countries that provide publicly funded residential care services for older adults.

Test case 3 focuses on private residential care in Italy, the Netherlands, and Australia. In Italy, the S4R Toolbox will be tested in a large facility with 450 employees. In the Netherlands and Australia, the S4R Toolbox will be tested in private residential care networks because of the structure of their health care systems. Australia will conduct an independent evaluation because of its complementary Australian funding.

Test case 4 represents the part of Europe where home care services and residential care homes are largely absent. In these settings, families provide care outside hospitals [14]. For this purpose, data will be collected in Romania, and the S4R Toolbox will be tested in an older adult care context representing the hospital-to-home interface. Health care services for older adults in Romania are provided primarily by hospitals, whereas public services to support patients in their homes are limited. Consequently, home care is typically provided by patients’ families. Recruiting a public hospital will therefore enable the project to investigate relevant aspects of older adult care within these types of health care systems.

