#### Pre-Post Evaluation (Test Cases 2-4)

Changes from baseline to postintervention will be examined using mixed-effects regression models. Individuals will be nested within organizational units, with random intercepts included for organizational units. Time will be entered as a fixed effect. Standardized effect sizes (Cohen *d*) will be calculated to aid interpretation.

For countries using a pre-post evaluation, a sample of 250-500 participants per country is sufficient to

Detect moderate changes (effect size, *d*≈0.25-0.36) with 95% power (taking clustering into account, assuming an intraclass correlation coefficient [ICC] of 0.05).Estimate within-country effects using mixed-effects models.Explore relevant subgroup differences.

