As a sensitivity analysis, we will use an algorithm to convert changes in SWEMWBS scores into WELLBY (Wellbeing-Adjusted Life Year) units [39-41]. WELLBYs have been monetized and can therefore provide a monetary estimate of effectiveness. This analysis will also provide an opportunity to interpret the results of the cost-effectiveness analysis across the range of willingness-to-pay values.

To further support the robustness of our analysis, we will also conduct a cost-benefit analysis. For this analysis, we will collect data from the participating organizations (work units) on sickness absence (spells and days), staff resignations, turnover, disability pensions, and personnel survey results for the years 2023-2026. Where possible, these measures will be monetized using national recommendations, statistics, reports, and research.

The S4R project does not aim to estimate a single pooled effect across countries. The participating health care systems differ substantially in structure, governance, workforce composition, and the availability of formal older adult care services. Because of this heterogeneity, the project follows the MRC guidance for evaluating complex interventions, which explicitly recommends that evaluation designs be adapted to local feasibility and contextual conditions.

In Norway and Finland, organizational structures allow randomization of home care units, making a cRCT feasible and appropriate for evaluating both effectiveness and cost-effectiveness. In the other participating countries, randomization was not feasible because of organizational differences and the absence of comparable units. For these countries, a pre-post evaluation is methodologically appropriate and enables examination of within-country change. This hybrid approach preserves scientific rigor by using the strongest possible design where feasible while ensuring validity and contextual relevance across diverse older adult care systems.

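### The Overview of the evaluation phase credits uncontrolled pre-post changes with assessing Toolbox effectiveness, an inference that only the randomized contrast supports and that the article elsewhere words more narrowly

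*Protocol article*

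**What the plan says.** Table 1 (Objectives) asks one evaluation question: "What are the relevance, effectiveness, and cost-effectiveness of the S4R Toolbox for improving the resilience and mental well-being of health care workers". The Overview of the implementation, evaluation and finalization phase answers it with two designs side by side: "We will assess the effectiveness of the S4R Toolbox through a cRCT (test case 1), a pre-post evaluation (test cases 2-4". It continues: "In both study designs, the primary outcome will be health care workers’ mental well-being, measured using the SWEMWBS".

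The pre-post section models change from baseline with a random intercept for organizational unit. On the term of interest it says: "Time will be entered as a fixed effect". One stated purpose of the sample of 250-500 per country is: "Estimate within-country effects using mixed-effects models". There is no comparison group.

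The pre-post countries appear under the description of the test cases. For Spain: "Test case 2 will take place in public residential care institutions and residential care institutions receiving public funding in Spain". For the next three: "Test case 3 focuses on private residential care in Italy, the Netherlands, and Australia". Romania is test case 4. Australia runs an independent evaluation.

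The end of the cost-effectiveness section describes the roles differently. It calls the cRCT suitable for evaluating effectiveness and cost-effectiveness, and says of the remaining countries: "For these countries, a pre-post evaluation is methodologically appropriate and enables examination of within-country change".

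**The concern.** The Overview makes no distinction between a randomized group difference and an uncontrolled before-after difference. Both are said to assess effectiveness, and both are attached to the same primary outcome. A reader following that section would accept a rise in SWEMWBS in Spain or Romania as evidence that the Toolbox works there, although the design cannot attribute the rise to the Toolbox.

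Other sections reinforce this reading. Study Design and Phases says that post-test data from the test sites will be used to assess effectiveness, and introduces the cRCT as an addition. Contextual Adaptation Across Europe expects the within-country evaluations to produce evidence on effectiveness. Strengths and Limitations names heterogeneity and the short time frame, but not the missing control group. What is at stake is an unsupported causal statement in reports to national and EU decision makers, the audience the Overview names.

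**Working it through.** **1. What each design estimates.** Let θ be the Toolbox effect and c the change in mean SWEMWBS that would have occurred anyway over the same interval.

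- cRCT: expected group difference = (θ + c) − c = θ, because randomization makes c equal in expectation in both arms.
- Pre-post: expected time coefficient = θ + c. Nothing in the model identifies c.

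A larger sample or an alpha adjustment does not remove c.

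**2. Whether c can be ignored.** Study Design and Phases places the pretest in the input phase, which spans months 1-17. The evaluation phase runs over months 22-43 and implementation takes 12 months. If the pretest falls at the end of month 17 and implementation starts at the beginning of month 22, four months pass before any Toolbox use. The interval to a post-test after full implementation is then at least 4 + 12 = 16 months. The documents give no reason to assume c = 0 over that time.

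**3. The sections side by side.**

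| Section | Role given to pre-post |
|---|---|
| Study Design and Phases | post-test data used to assess effectiveness and cost-effectiveness |
| Evaluation phase, Overview | assesses effectiveness, same primary outcome as the cRCT |
| Pre-Post Evaluation | estimates within-country effects through a time term |
| Cost-Effectiveness Analysis | examines within-country change; cost-effectiveness confined to the cRCT |
| Contextual Adaptation | contributes evidence on effectiveness, with Norway and Finland singled out |

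Only the Cost-Effectiveness Analysis section fits the design.

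**4. The planning figures.** No alpha is stated; two-sided 5% is assumed.

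- cRCT, with 15 clusters of 9 per arm (135), design effect 1 + 8 × 0.05 = 1.40, and the mean of five follow-ups adjusted for baseline: d = (2.048 + 1.701) × √(2 × 1.40 × f / 135), with f = (1 + 4r)/5 − r². For r = 0.7, f = 0.27 and d = 0.281. For r = 0.5, f = 0.35 and d = 0.319. Stated: 0.28-0.32.
- Pre-post, assuming r = 0.5 and 30 respondents per unit (design effect 1 + 29 × 0.05 = 2.45): d = (1.960 + 1.645) × √(2 × 0.5 × 2.45 / N) = 0.357 at N = 250 and 0.252 at N = 500. Stated: 0.25-0.36. The article does not give these two inputs, so the match shows only that the range is attainable.

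The problem is therefore not in the power figures.

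**5. Illustration for one country.** The implied standard error is d/(1.960 + 1.645): 0.25/3.605 = 0.069 and 0.36/3.605 = 0.100. With θ = 0, P(significant benefit) = 1 − Φ(1.960 − c/SE).

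| Assumed c (SD) | SE 0.100 | SE 0.069 |
|---|---|---|
| 0 | 0.025 | 0.025 |
| 0.05 | 0.072 | 0.108 |
| 0.10 | 0.169 | 0.302 |

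The size and sign of c are assumptions; the documents give neither. The 250-500 total also includes leaders and informal caregivers, whereas the primary outcome is measured in health care workers. The real standard error would be larger, and the probabilities for an upward drift lower.

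**The case against.** The strongest reply is that the article already ranks the designs. The cost-effectiveness section links effectiveness to the cRCT, describes the approach as using the strongest design that each setting allows, and limits pre-post to within-country change. Only the cRCT has intention-to-treat, complier and cost-effectiveness analyses. Evaluation and Policy Relevance also points to Norway and Finland in particular. This stands as a partial, implicit hierarchy. It does not cure the Overview, which states the opposite role for pre-post in the place where the primary outcome is set.

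A reader might infer more: that there are six primary tests, that any positive country could override a null cRCT, and that the error rate is inflated accordingly. The documents do not support that. They name one primary outcome in two designs, not six confirmatory tests. They decline to pool across countries and state no rule under which any single positive result counts as success. The settings differ, so a null result in Nordic home care and a rise in Spanish residential care would not formally contradict each other. A family-wise figure, such as 1 − 0.975⁵ = 11.9% for five countries (9.6% for four) in the favourable direction, presumes independence and a joint claim that the article does not make.

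It can also be said that multiplicity and the reading of discordant results belong in an analysis plan that is not shown. That is fair, and neither is raised here. It is also true that relabelling would leave the drift probabilities unchanged; what changes is the claim attached to a significant time effect.

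**Conclusion.** The point holds in a limited form. The Overview, with echoes in Study Design and Phases and in Contextual Adaptation Across Europe, attributes to the pre-post evaluation an inference about effectiveness that an uncontrolled time effect cannot carry. The cost-effectiveness section gives it the weaker role that the design does support. The inconsistency touches the primary-outcome analysis in Spain, Italy, the Netherlands, Romania and, under its own evaluation, Australia.

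This conclusion rests on the text and the design, not on a numerical error: the sample-size figures can be reproduced. The 7-11% (0.05 SD) and 17-30% (0.10 SD) single-country probabilities are illustrations under an assumed alpha, an assumed upward drift and the stated precision. They should not be read as the plan's error rate.

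**What to change.** In the Overview, name the cRCT group contrast on SWEMWBS as the confirmatory test of Toolbox effectiveness. Describe the estimates from test cases 2-4 as supportive evidence of within-country change, reported with 95% confidence intervals and without a causal effectiveness claim. Bring Study Design and Phases and Contextual Adaptation Across Europe into line with this; in the former, the reference to cost-effectiveness should also match its restriction to Norway and Finland. The absence of a control group in test cases 2-4 could be added to the limitations.

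The cost is a few sentences, with no new data or analysis. The downside is that test cases 2-4 could then report change but not, on their own, effectiveness. Implementation was scheduled to begin in April 2026, so the wording should be settled before post-intervention outcomes are seen.
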